## Abstract

**Introduction::**

The main cause of anastomotic leakage (AL) is tissue hypoxia, which results from impaired perfusion of the pedicle stomach graft after esophageal reconstruction. Clinical judgment is unreliable in determining graft perfusion. Therefore, an objective, validated, and reproducible method is urgently needed. Near infrared fluorescence perfusion imaging using indocyanine green (ICG) is an emerging and promising modality. This study's objectives are to evaluate the feasibility of quantification of ICG angiography (ICGA) to assess graft perfusion and to validate ICGA by comparison with hemodynamic parameters, blood and tissue expression of hypoxia-induced markers, and tissue mitochondrial respiration rates. And, second, to evaluate its ability to predict AL in patients after minimally invasive esophagectomy (MIE).

**Methods::**

Patients (N = 70) with resectable esophageal cancer will be recruited for standard MIE. ICGA will be performed after graft creation and thoracic pull-up. Dynamic digital images will be obtained starting after intravenous bolus administration of ICG. The resulting images will be subjected to curve analysis and to compartmental analysis based on the adiabatic approximation to tissue homogeneity kinetic model. The calculated perfusion parameters will be compared to intraoperative hemodynamic data to evaluate the effects of patient hemodynamics. To verify whether graft perfusion represents tissue oxygenation, ICGA perfusion parameters will be compared with systemic and serosa lactate from the stomach graft. In addition, perfusion parameters will be compared to tissue expression of hypoxia-related markers and mitochondrial chain respiratory rate. Finally, the ability of functional, histological, and cellular perfusion and oxygenation parameters to predict AL and postoperative morbidity in general will be evaluated using the appropriate univariate and multivariate statistical analyses.

**Discussion::**

The results of this project may lead to a novel, reproducible, and minimally invasive method to objectively assess perioperative anastomotic perfusion during MIE, potentially reducing the incidence of AL and its associated severe morbidity and mortality.

**Trial registration::**

Clinicaltrials.gov registration number is NCT03587532. The study was approved by the ethical committee of the Ghent University, Belgium (B670201836427).

## Introduction

1

### Esophagectomy

1.1

Over the past 2 decades the incidence of adenocarcinoma of the esophagus is rapidly increasing.^[1]^ Despite extensive changes in therapeutic modalities surgical resection remains the cornerstone in therapy for curable esophageal cancer (EC). After the esophagectomy, the stomach is most commonly used to restore continuity of the upper gastro intestinal tract. However, anastomotic sites are prone to serious complications such as leakage, fistulas, bleeding, and strictures. Anastomotic leakage (AL) remains one of the main causes of postoperative morbidity and mortality in digestive surgery. The reported leakage incidence after esophagectomy ranges from 5% to up to 20%.^[2–6]^ The leak-associated mortality is 18% to 40% compared with an overall in-hospital mortality of 4% to 6%.^[2,7,8]^ Several risk factors for AL have been identified.^[2–11]^ The perfusion of the anastomosis is generally considered to be an important predictor for anastomotic integrity. During surgery the clinical judgment of the surgeon determines the anastomotic region's viability based on subjective parameters as color and vessel pulsation. A good noninvasive method to objectively assess viability and perfusion of the anastomotic site could help the surgeon to reliable decide the appropriate anastomotic region.

### Perfusion assessment methods

1.2

Several methods have been tested to intraoperatively evaluate graft's perfusion, such as Laser speckle contrast imaging, gastric tonometry, Doppler flowmetry, spectroscopy, and angiography.^[12–15]^ None of them have been widely accepted due to different reasons. Most of these methods could differentiate well-perfused from hypoperfused tissue but failed to give quantitative physiological information on vascular perfusion. Angiography is a widely used easy, intraoperative tool to provide structural information on vascularization. Quantifying angiography would combine the advantages of a structural imaging with the necessary info needed from a functional perfusion analysis.

### NIRF imaging with ICG

1.3

Indocyanine green angiography (ICGA) is an emerging medical imaging modality requiring a fluorescence-imaging agent that can be excited at near infrared (NIR) wavelengths. Penetrating NIR light excites a near-infrared fluorescence (NIRF) agent generating fluorescence that can be captured by adapted cameras to create a 2D image of tissue deposition of the NIRF imaging agent. Indocyanine green (ICG) is a clinically used NIRF agent with excellent safety records. Its absorption maximum around 760 to 780 nm, its confinement to the vascular compartment (due to binding with plasma proteins), its low toxicity, and its rapid and almost exclusive biliary excretion has added to the rapid Food and Drug Administration approval for clinical use in 1956. ICG has been used intraoperative in neurosurgical, coronary, vascular, and reconstructive surgeries as a nonspecific blood vascular imaging agent to assess organ perfusion.^[16]^

### ICGA-guided esophageal surgery

1.4

Objective, in-depth assessment of tissue perfusion using NIR imaging during creation of the esophagogastric anastomosis in EC surgery has not been previously reported. Most studies aiming to measure intraoperative tissue perfusion during surgery have used invasive probes or methods that sample only a small tissue volume. Several pilot studies were published that report promising results of NIRF-based perfusion imaging during EC surgery.^[17–20]^ However, these were feasibility studies, and did not encompass any attempts to calculate physiologically relevant parameters, quantify perfusion, or validate imaging findings by comparison with a criterion standard.^[17–24]^

## Methods and analysis

2

### Study design

2.1

This is a prospective, single-center, in vivo, observational study on 70 patients undergoing minimally invasive esophagectomy (MIE) with a pedicle gastric graft reconstruction in the department of digestive surgery at the University Hospital of Ghent. ICGA images perfusion measurements, blood samples, and biopsies will be obtained after creation of the gastric tube and before the esophagogastric anastomosis. Dynamic ICGA digital images will be obtained and subjected to curve analysis and to compartmental analysis based on the adiabatic approximation to tissue homogeneity (AATH) kinetic model. The calculated imaging based perfusion assessment of the stomach graft will be compared to intraoperative hemodynamic data and validated using tissue, serum, and cellular hallmarks of hypoperfusion and hypoxia. Finally, the ability of functional, histological, and cellular perfusion and oxygenation parameters to predict AL and postoperative morbidity in general will be evaluated using the appropriate univariate and multivariate statistical analyses.

The methodology was developed according to the strengthening the reporting of observational studies in epidemiology (STROBE) and the statement for reporting studies of diagnostic accuracy (STARD) guidelines. The protocol was written based on the Standard protocol items for clinical trials (SPIRIT) checklist.

### Study objectives and endpoints

2.2

The primary endpoint will be to determine an ICGA-based cutoff point to predict AL and graft necrosis after esophageal reconstructive surgery. This cutoff value will be an ICGA fluorescent intensity time measurement expressed in seconds.

Secondary endpoints are the following:

The evaluation of ICGA as a quantitative perfusion imaging modality during gastric tube reconstruction. First, intensity over time curves will be analyzed in the regions of interest to generate quantitative values for maximal fluorescence intensity (*I*_max_), inflow time (*T*_inflow_), and outflow time (*T*_outflow_). Second, a kinetic modeling analysis of the time-varying ICG concentration images will be performed, based on a tracer kinetic model that was developed to measure tissue blood flow and vascular permeability.The validation of ICGA imaging by comparing the quantitative data:

To continuous perioperative hemodynamic measurements from a Pulse index Continuous Cardiac Output (PiCCO) catheter.To biological markers of hypoxia and ischemia: systemic and capillary lactate levels (measured in systemic and serosal blood samples) and mitochondrial chain respiratory rates (measured on tissue biopsies).And to histopathological ischemic markers of hypoxia and ischemia.Patient outcome in terms of AL and necrosis defined by the Esophagectomy Complications Consensus Group (ECCG) classification and identified by clinical and radiological methods. Based on a receiver operating curve we hope to determine a cut-off value for the prediction of gastric graft malperfusion.Product-related toxicity.Surgery-related endpoints: number of crossover patients: perioperative change of anastomotic site based on ICG findings, perioperative blood loss, and perioperative adverse events.Incidence of minor and major adverse events up to 30 days postoperatively classified by the Clavien-Dindo score and based on the ECCG international consensus for complications associated with esophagectomy.^[25]^Intensive care unit and in hospital stay and finally incidence of stricture up to 1 year postoperatively.

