### Study population

2.3

All nonmetastatic EC patients aged ≥18 years and scheduled for elective MIE with an intrathoracic stapled esophagogastric anastomosis will be screened for inclusion and exclusion criteria. Once potentially eligible, study procedures will be explained to the candidate and participation will be offered. Subjects willing to participate must be physically and mentally fit for surgery, and need to sign an informed consent after a consent process and before any study-related procedures may take place. Surgery must be within 90 days of signing the informed consent. Patients will be excluded in case of known hypersensitivity to ICG. Female patients who are pregnant or nursing, patients participating in other studies involving investigational drugs or devices, and patients with documented use of Avastin (bevacizumab) or other anti-vascular endothelial growth factor agents within 30 days before surgery. During surgery exclusion criteria will be reanalyzed and patients will be excluded in case of intraoperative findings that may preclude conduct of the study procedures, when anastomosis is performed differently than the standard of care and in case of excessive bleeding (>500 mL) before anastomosis.

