#### Surgical procedure

2.5.1

A standard MIE will be performed using the Ivor Lewis technique (intrathoracic stapled esophagogastric anastomosis). Three regions of interest (ROIs) will be marked on the stomach graft with a suture (Fig. 1):

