**Figure 1 F1:**
[figure not shown]
The regions of interest during gastric tube construction.

ROI 1: well perfused control region: 2 to 3 cm proximal to the pylorus

ROI 2: clinically identified anastomotic site: study region

ROI 3: ischemic control region: in the proximal (excluded) stomach

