#### ICG-based NIR perfusion imaging

2.5.2

Imaging will be performed twice: 30 minutes after the creation of the stomach graft (in the abdomen), and immediately before creation of the esophagogastric anastomosis (in the right thorax). A dose of 0.5 mg/kg of ICG (ICG-Pulsion, Pulsion Medical Systems, Munich, Germany) will be injected as an intravenous bolus. Images will be recorded starting immediately before injection until 3 minutes afterwards. Video data will be obtained with a charge-coupled device camera fitted with a light-emitting diode emitting at a wavelength of 760 nm, and the appropriate filters to detect NIR fluorescence (Visera elite II, Olympus Medical System Corp, Tokyo, Japan). The fluorescence signals are sent to a digital video processor to be displayed on a TV monitor in real time (Fig. 2).

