### Statistical analysis

2.7

Study data will be collected in an excel data collection sheet, in which descriptive statistics can be provided for all measured parameters. Quantitative data are expressed as mean and/or median with standard deviation, interquartile range, or min-max range. Data will be analyzed using standard statistical software (SPSS version 22 for windows, SPSS Inc, Chicago, IL). An ROC curve for sensitivity and specificity for leakage as binary classifier will be constructed. From this curve, the Youden index will be used to calculate a best-fit cut-off point. Statistical analysis using chi-square test, Fisher exact test, and Mann-Whitney *U* test will be performed whenever needed. A *P* value <0.05 is considered statistically significant.

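### ICGA is shown live and may move the anastomosis, while the study region is the clinically chosen, suture-marked site. In moved patients the reading and the leak outcome can belong to different tissue, which biases the ROC and its cutoff.

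*Protocol article*

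**What the plan says.** Section 2.2 (Study objectives and endpoints) sets the primary aim: "The primary endpoint will be to determine an ICGA-based cutoff point to predict AL and graft necrosis after esophageal reconstructive surgery". The cutoff is a time in seconds. Section 2.7 (Statistical analysis) says how it is obtained: "An ROC curve for sensitivity and specificity for leakage as binary classifier will be constructed", followed by the Youden index.

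Four other statements bear on what that ROC will measure:

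- Section 2.5.2 (imaging): "The fluorescence signals are sent to a digital video processor to be displayed on a TV monitor in real time". The article describes no masking of the surgeon.
- Section 2.2, among the surgery-related endpoints: "number of crossover patients: perioperative change of anastomotic site based on ICG findings". Acting on the images is therefore foreseen.
- Section 2.5.1 (surgical procedure): "Three regions of interest (ROIs) will be marked on the stomach graft with a suture". The Figure 1 legend defines the one that matters here: "ROI 2: clinically identified anastomotic site: study region".
- Section 2.5.2 again: there are two recordings, one in the abdomen after the graft is made and one in the thorax just before the anastomosis. Both come before the join.

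Section 2.1 calls the study observational. Section 2.3 (Study population) excludes patients during surgery "when anastomosis is performed differently than the standard of care" and does not mention ICG-driven site changes.

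**The concern.** An ROC curve against leakage estimates predictive accuracy only if the reading describes the tissue that could leak, and if the reading did not itself alter the chance of a leak. The stated design can break both conditions in the same patients.

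If the surgeon moves the anastomosis because of the fluorescence, the value at the clinically chosen ROI 2 belongs to tissue that was not joined, while the leak outcome belongs to another site. If the move helps, a poor reading is paired with no leak. That counts against ICGA in exactly the patients where it was useful. Sensitivity and AUC fall, the Youden cutoff shifts towards less abnormal values, and there are fewer leaks to analyse. At stake are the primary endpoint itself and the power of section 2.4.

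**Working it through.** **1. The plan's own sample size.** Section 2.4 gives alpha 0.05, power 0.80, 16% leaks and 54 patients, but neither the AUC assumed nor the sidedness. With the Hanley-McNeil variance, testing against AUC 0.50 two-sided, an AUC of 0.79 needs 56 patients and 0.80 needs 52. So 54 corresponds to about 0.79 to 0.80. One-sided, 0.76 needs 55. I take 0.79 two-sided as the working value. Evaluable patients: 70 × 0.90 = 63, with 63 × 0.16 = 10.1 expected leaks.

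**2. Formula.** With n1 leaks and n0 non-leaks, Q1 = A/(2 − A) and Q2 = 2A²/(1 + A):

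SE(A)² = [A(1 − A) + (n1 − 1)(Q1 − A²) + (n0 − 1)(Q2 − A²)] / (n1·n0)

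Power = Φ{[(A − 0.5) − 1.96·SE(0.5)] / SE(A)}

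No patients moved, A = 0.79, n1 = 10.1, n0 = 52.9: SE(0.5) = 0.100, SE(0.79) = 0.089, and (0.29 − 0.196)/0.089 = 1.06, so power is about 86% (85% if A is rounded to 0.79).

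**3. Model for moved patients.** These are assumptions; the article gives no crossover share or effect.
- The reading x is standard normal and logit P(leak) = a + 1.28x, with a set to give 16% leaks. The true AUC is 0.79.
- The surgeon acts on a visual impression that has correlation r with x. The share q with the worst impression is moved.
- A moved patient takes the leak risk of a value drawn from the patients not moved.
- The ROC uses x at the original ROI 2, with n = 63.

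**4. Results, as AUC at the original ROI 2 / power.**

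| Share moved | r = 1 (worst case) | r = 0.8 | r = 0.6 |
|---|---|---|---|
| 0% | 0.79 / 86% | 0.79 / 86% | 0.79 / 86% |
| 5% | 0.74 / 60% | 0.76 / 70% | 0.77 / 76% |
| 10% | 0.70 / 42% | 0.73 / 57% | 0.75 / 66% |
| 20% | 0.64 / 20% | 0.69 / 38% | 0.72 / 50% |

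Hand check of the 10%, r = 1 cell: the leak rate is 12%, so n1 = 7.6 and n0 = 55.4. SE(0.5) = 0.113 and SE(0.70) = 0.112, and (0.20 − 0.221)/0.112 = −0.19, giving about 42%.

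**5. A second model for direction.** This is a binormal model with true AUC 0.75 or 0.80, in which the worst 5% to 20% are moved and 25% to 75% of their leaks averted. The AUC falls by about 0.02 to 0.14, and the Youden cutoff moves towards less abnormal values in every case. At true AUC 0.80 with 10% moved and half their leaks averted, it goes from 0.59 to 0.40 SD of the non-leak group.

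**6. What re-reading at the actual site recovers.** In the r = 1 case, using the value at the site actually joined gives AUC about 0.745 and power about 59% at 10% moved, and 0.72 and about 41% at 20% moved. The region mismatch goes. The loss of spread and of events does not.

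**The case against.** Several points on the other side are fair.

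- **Re-marking is not ruled out.** The article does not say that ROI 2 stays put after a site change, nor which ROI or recording feeds the ROC. This stands as a limit. A clinically identified site marked by suture naturally means the original site, but that is a reading of the text.
- **The surgeon does not see the index value.** The time in seconds comes from curve analysis of stored video (sections 2.6.2 and 2.6.3). A reader might infer that the patients with the worst ROI 2 readings are the ones moved; the documents do not say so. A correlated visual impression is enough for bias, but the r = 1 column is a worst case.
- **Crossovers may be rare or absent.** This stands, and with none there is no bias. But with about 10 leaks expected, one or two averted leaks matter.
- **Leaks below 16%.** A reader might infer that site changes push the leak rate under the planning figure. Section 2.4 says only that 16% is to be observed, so it may already describe practice with ICGA. The illustration treats it as the rate without moves, which is an assumption.
- **Exclusion of moved patients.** A reader might infer that section 2.3 removes them. A site change along the graft can remain the same Ivor Lewis stapled anastomosis, and counting crossovers as an endpoint suggests they are kept. The wording is unclear, and no more than that.
- **Analysis handling belongs in an SAP.** This holds for the detail of sensitivity analyses. It does not answer the design point: live display, foreseen action on it, and a study region defined by the clinical site are all stated here.

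**Conclusion.** The concern holds as a design defect in stated rules. Followed as written, a moved patient contributes a reading from one piece of tissue and an outcome from another, and the test may have altered the outcome. The ROC, AUC and Youden cutoff are then biased, most likely towards a lower AUC.

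The size cannot be fixed from the article. It runs from nothing, with no crossovers, to an AUC of 0.64 to 0.72 and power of 20% to 50% if 20% are moved. These figures rest on a true AUC of 0.79, 16% leaks without moves, 63 evaluable patients, moves that lower risk, and a correlation between 0.6 and 1 of visual impression with quantified reading. The lower end of each range should not be quoted as the expected loss.

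This should be fixed; confidence is moderate.

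**What to change.** - In sections 2.2 and 2.7, define the reading for the primary ROC as that of the site actually anastomosed, taken from the stored thoracic recording where that site can be identified.
- In section 2.3, state that an ICG-driven site change is not by itself an exclusion from the study, consistent with counting crossovers as an endpoint.
- Report moved patients separately. Repeat the ROC without them, and with the original ROI 2 value. Leaving them out is itself selection on the test, so it is a sensitivity analysis only.
- State that the AUC and cutoff are conditional on live display of the images.
- Reconcile the observational label in section 2.1 with a test result that can alter the operation.

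The cost is some extra image reading and analysis. The recording was made before the join, so the final site may not be identifiable in every patient; that number should be reported. Residual bias from acting on the test remains and must be stated as a limitation.

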### Study population

2.3

All nonmetastatic EC patients aged ≥18 years and scheduled for elective MIE with an intrathoracic stapled esophagogastric anastomosis will be screened for inclusion and exclusion criteria. Once potentially eligible, study procedures will be explained to the candidate and participation will be offered. Subjects willing to participate must be physically and mentally fit for surgery, and need to sign an informed consent after a consent process and before any study-related procedures may take place. Surgery must be within 90 days of signing the informed consent. Patients will be excluded in case of known hypersensitivity to ICG. Female patients who are pregnant or nursing, patients participating in other studies involving investigational drugs or devices, and patients with documented use of Avastin (bevacizumab) or other anti-vascular endothelial growth factor agents within 30 days before surgery. During surgery exclusion criteria will be reanalyzed and patients will be excluded in case of intraoperative findings that may preclude conduct of the study procedures, when anastomosis is performed differently than the standard of care and in case of excessive bleeding (>500 mL) before anastomosis.

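### Intraoperative exclusions in section 2.3 can fall after ICG has been given and partly on an endpoint; patients already exposed should be kept in the toxicity, adverse-event, blood-loss and crossover summaries

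*Protocol article*

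**What the plan says.** All references are to the protocol article.

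- **Study population (2.3)** re-applies the exclusion criteria in the operating room: "During surgery exclusion criteria will be reanalyzed and patients will be excluded in case of intraoperative findings" that prevent the study procedures, "when anastomosis is performed differently than the standard of care", and "in case of excessive bleeding (>500 mL) before anastomosis". The rule carries no qualification about which analyses it governs.
- **ICG-based NIR perfusion imaging (2.5.2)** fixes the timing: "Imaging will be performed twice: 30 minutes after the creation of the stomach graft (in the abdomen), and immediately before creation of the esophagogastric anastomosis", the latter in the right thorax. The dye "will be injected as an intravenous bolus". Under section 2.5.4, blood and tissue samples are taken directly after each imaging moment.
- **Study objectives and endpoints (2.2)** lists among the secondary endpoints "Product-related toxicity", the number of crossover patients (anastomotic site changed because of ICG findings), and "perioperative blood loss, and perioperative adverse events".
- **Sample size (2.4)** requires 54 patients at an observed leak rate of 16%, allows 10% for dropout or loss to follow-up, and enrols 70. Intraoperative exclusion is not mentioned there.

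**The concern.** Two features of the rule matter.

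First, it can act after exposure. A toxicity summary should cover everyone who received the product. If patients leave the study between receiving ICG and the anastomosis, the denominator becomes those whose operation followed the standard course up to that point.

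Second, it acts partly on the endpoints themselves. Blood loss is an endpoint, and a high value of its pre-anastomotic part is a reason for exclusion. Change of anastomotic site because of ICG is also an endpoint. If such a change leads to an anastomosis that counts as non-standard, the patient who should be counted is the one excluded.

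At stake is whether the safety, blood-loss and crossover results describe all patients given ICG or only a selected part of them.

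**Working it through.** **1. Order of events**

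| Step | Source | ICG already given? |
|---|---|---|
| Graft created in the abdomen | 2.5.2 | No |
| First imaging with ICG, 30 minutes later, then samples | 2.5.2, 2.5.4 | Yes |
| Second imaging in the thorax, then samples | 2.5.2, 2.5.4 | Yes |
| Anastomosis made | 2.5.2 | Yes |

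*Bleeding rule.* The window runs up to the anastomosis. Bleeding that passes 500 mL before the first session leads to exclusion before exposure. Bleeding that passes it later leads to exclusion after exposure. Both are possible under the text.

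*Non-standard anastomosis rule.* Departure from standard is certain only when the anastomosis is made, normally after both sessions.

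**2. Endpoint against rule**

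- *Toxicity and adverse events:* no value of these endpoints triggers exclusion, but exposed patients can leave the denominator.
- *Blood loss:* let B be the loss before anastomosis. Exclusion applies when B > 500 mL, so every retained patient has B ≤ 500 mL. This follows from the wording and needs no assumed rate. Loss from the anastomosis onward is not capped.
- *Crossover:* a patient moved because of ICG is counted under 2.2, but is excluded under 2.3 if the result counts as non-standard. The article does not say whether it does.

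**3. How many exposed patients could be affected**

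The article gives no exclusion rate. Assume, for illustration only, 5% to 10% of the 70 are excluded after the first bolus:

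- 70 × 0.05 = 3.5; 70 × 0.10 = 7.
- With 7 excluded, the toxicity denominator falls from 70 to 63. A single toxic event among those 7 would be 1/70 = 1.4% of exposed patients but would appear as 0/63.

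**4. Does the ROC analysis lose too many patients?**

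Reproducing the plan's figure first: 54 / 0.90 = 60, and 54 × 1.10 = 59.4, also rounding up to 60. Neither gives the stated 70. That mismatch is a separate matter; here it only means there is slack of 10 patients.

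- 70 × 0.90 = 63 after dropout.
- 63 − 4 = 59 and 63 − 7 = 56, both above 54.
- Largest exclusion fraction e that still leaves 54: 70 × (1 − e) × 0.90 = 54, so e = 1 − 60/70 = 14.3%, or 10 of 70.

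**5. Does the ROC analysis lose leaks?**

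Expected leaks: 70 × 0.16 = 11.2. If excluded patients leaked at an assumed 16% to 30%, the loss would be between 4 × 0.16 = 0.6 and 7 × 0.30 = 2.1 leaks. Neither the exclusion rate nor the raised leak risk has a source in the article, so this range is not evidence of bias.

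**The case against.** The strongest reply is that section 2.3 describes the study population, and that nowhere does the article say that an excluded patient leaves the toxicity or adverse-event summaries. Being excluded could mean not evaluable for the ROC curve, replaced, or removed altogether, and analysis sets are commonly left to a full protocol or analysis plan, which is not shown. This stands in part. A reader might infer that exposed patients are certainly dropped from safety reporting; the text does not go that far, so the point is that they may be. It does not dispose of the matter, because 2.3 states the exclusion without qualification. Followed as written, it removes exposed patients and truncates an endpoint.

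A second reply is that the restriction is deliberate. The cutoff is meant for a standard intrathoracic stapled anastomosis, and both excluding other anastomoses and limiting bleeding before the leak outcome define where it applies. This stands for the ROC analysis.

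A third reply is that the blood-loss point is small: only the pre-anastomotic part is capped, and it is one of many secondary endpoints in a single-center observational study with no planned test on it. That is fair as to weight, but the truncation is real.

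Finally, it would be too strong to say that safety is seen only where surgery went well, or that the hemodynamic aim is defeated. Retained patients can still leak, have adverse events or develop strictures, and continuous PiCCO monitoring still records hemodynamic variation among them.

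**Conclusion.** The concern holds for the toxicity, adverse-event, blood-loss and crossover endpoints. As worded, section 2.3 allows patients to be excluded after ICG, and one of its criteria is a value of an endpoint. The cap on pre-anastomotic blood loss at 500 mL is certain on the plain wording. Selection in the toxicity and adverse-event summaries is possible and depends on what exclusion is taken to mean. Loss from the crossover count depends on whether an ICG-driven change of site counts as non-standard. The size of the affected group is unknown; 3.5 to 7 of 70 rests wholly on an assumed 5% to 10%.

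A reader might go on to infer that the ROC analysis is underpowered, or that the AUC and leak rate are distorted. The documents do not support this. Enrolment of 70 absorbs up to 14.3% intraoperative exclusion on top of 10% dropout, the restricted population is a defensible target, and a higher leak risk among excluded patients is only an assumption.

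**What to change.** In sections 2.3 and 2.7, state that:

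1. the intraoperative exclusions apply only to the ROC and cutoff analysis;
2. every patient given ICG remains in the toxicity, adverse-event, blood-loss and crossover summaries;
3. the number of intraoperative exclusions is reported, with the reason for each and whether ICG had already been given.

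Sections 2.2 and 2.3 should also be reconciled on whether a change of site prompted by ICG counts as a non-standard anastomosis.

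The ROC population can stay restricted as planned. An optional sensitivity analysis could add back excluded patients who have an ROI 2 recording and an esophagogastric anastomosis; its price is a more mixed set of anastomoses, which is why it should not replace the main analysis.

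The cost is a few sentences, follow-up data from the same hospital record on a few more patients, and one extra table if the sensitivity analysis is done. The change alters no study procedure or clinical rule.
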